### Data Collection

For this study, we will collect data through interviews (A–C) and repeated web-based questionnaires (D). In studies A and B, interviews will be conducted with parents individually or with two parents within a couple relationship together, depending on the preference of the parents. In cases when interviews are held with the parental couple together, their listening to each other may make them aware of things they might not otherwise have reflected on, which might contribute to broader narratives. In study C, focus-group interviews with healthcare professionals will be conducted. Interviews will be held when the participants have had access to the intervention (*Childbirth Journey* or *Interplay*) for ~2 weeks. Interviews will follow interview guides with questions regarding user experience and usage of the serious games according to such themes as trustworthiness, usefulness, support, knowledge, and feelings related to labor, parenthood, and parental couple relationships. Examples of questions are as follows: “*Please describe your experiences from using* Childbirth Journey”, “*Did you perceive it as easy to understand?*”, “*Has* Childbirth Journey *affected you somehow in your preparation for labor?*” (study A); “*Has* Interplay *affected your couple relationship somehow?*”, “*Did you experience* Interplay *as a support in your couple relationship or parental role?*” (study B) and “*Will you offer* Childbirth Journey *(or* Interplay*) for expectant parents?*” (study C). Follow-up questions will be used, such as “*Could you please tell me more about that?*” and “*Please describe this further*”. Besides questions regarding the participants' previous experience from using serious games will be included in the interview guides. The interview guides have been pilot tested with results showing that the interview questions were easy to understand and respond to, by the interviewed. The pilot interviews will not be included in the data analysis in each study (A–C). The interviews will be held by researchers with doctoral degrees and previous experience in qualitative methods, as well as individual and focus-group interviews. The interviews will be audio-recorded and transcribed verbatim.

In study D, participants will complete a web-based questionnaire at baseline (Q1) before receiving the intervention. Another web-based questionnaire (Q2) will be sent to the participants 6 months after Q1. Two reminders will be sent to participants who do not complete Q1 or Q2; the reminders will be sent at 1-week intervals. Since study D will be based on the results of studies B and C, the measures and questions to be included in the questionnaires will be decided after publication of this study protocol; however, questions regarding participant socio-demographics will be included in Q1, which is important since this is a national survey. In addition, some previously validated measures will be included in both Q1 and Q2, as described below. Since *Interplay* includes concrete tasks and learning elements aiming to strengthen expectant and new parents in their knowledge and ability to handle their role as partners, we will include the QDR36 questionnaire (36) in Q1 and Q2. The QDR36 consists of 36 items covering five different dimensions of the parent dyad: *consensus, cohesion, satisfaction, sensuality*, and *sexuality*. In addition, parents' perceived quality of the couple relationship has previously been shown to be associated with their sense of coherence [SOC; (37)]; therefore, the validated Swedish version (38) of the SOC-13 (39) will be included in Q1 and Q2. SOC-13 consists of 13 items covering three different dimensions, comprising parents' senses of *comprehensibility, manageability*, and *meaningfulness*. Furthermore, parents' perceived quality of the couple relationship has previously been shown to be associated with their perceived social support (37). Therefore, the Swedish version (40) of the multidimensional scale of perceived social support [MSPPS; (41)] will be included in the questionnaires (Q1–Q2) to assess the parents' perceived social support. The scale consists of 12 items that cover three different dimensions of social support—support from *family, friends*, and *significant others*. The measures included in the questionnaires for this study are published elsewhere.

For studies B–D, log data for process evaluation purposes during the intervention will be collected. These data will be utilized to evaluate the usage of the mobile application; for example, through login and logout times, the activities completed, and the time spent studying each content area or answering questions related to it. Only pre-specified log data will be collected, and they will not contain any information that can be used to identify individual participants. This means that IP addresses will not be recorded. Participants' mobile application usage will only be studied and presented through aggregated metrics, such as average session duration.

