## Objectives

The overall aim of the prospective study is to explore two different serious games, which are as follows: (1) *Childbirth Journey* (Swedish title: *Förlossningsresan*), relating to pregnancy, childbirth and parenthood; and (2) *Interplay* (Swedish title: *Samspel*), relating to parental couple relationships and parenthood. The secondary aims of the prospective study are to explore the following:

(1) Parents' perceptions of and user behavior in *Childbirth Journey*. Research question: How do parents perceive *Childbirth Journey* as a digital parental support relating to pregnancy, childbirth and parenthood? (Study A).(2) Parents' perceptions of and user behavior in *Interplay*. Research question: How do parents perceive *Interplay* as a digital parental support relating to parental couple relationships and parenthood? (Study B).(3) Healthcare professionals' perceptions of *Childbirth Journey* and *Interplay*. Research questions: (1) How do healthcare professionals perceive *Childbirth Journey* as a digital support for parents relating to pregnancy, childbirth and parenthood, and (2) How do healthcare professionals perceive *Interplay* as a digital support for parents relating to parental couple relationships and parenthood? (Study C).(4) Parents' user behavior over time and individual sessions in *Interplay*, as well as their perceived quality of the parental couple relationship, social support, and sense of coherence related to the results in study A–C (study D).

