#### Interplay

The second serious game that will be explored for this study, *Interplay*, represents another game genre, the casual quiz game (33), where competition is a catalyst for social interaction. Many similar games contain puzzles that the player must solve to progress. These can potentially provide the player with an interesting challenge, but they may also stop a player from continuing. However, *Interplay* does not pose any real obstacles to player progression, as by focussing on the core aesthetics of the genre, we reduce the risk that some players might become stuck. *Interplay* has been used by many players in its Danish version (Danish title: *Samspil*), so the design is well tested, although it has not been explored in any research study.

In preparation for this study, the Danish version has been translated to Swedish and revised to be suitable within the Swedish context. *Interplay* includes concrete tasks and learning elements that aim to strengthen expectant and new parents' knowledge and ability to handle their role as partners and parents. The intention is that parents should use *Interplay* to help in creating a safe and well-functioning environment for them and their children. Since *Interplay* is provided digitally, this enables parents to use it without hindrance, regardless of time and space.

In study B, expectant parents and new parents will take part in the intervention, and their experiences from and user behavior in *Interplay* will be explored. In study C, healthcare professionals will take part in the intervention, and their experiences of *Interplay* will be explored. The results of study B and C will contribute with further development of the *Interplay* before conducting study D. In study D, expectant and new parents will take part in the intervention, and their user behavior over time and individual sessions in *Interplay*—as well as associated factors between parents' user behavior and experiences from *Interplay* and their perceived quality of parental couple relationships, social support, and sense of coherence—will be explored.

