
## Ethics and Dissemination

Interventions included in this study are considered low-risk interventions. A limited number of expected negative experiences for the participants may become relevant. These may relate to usage of the serious games, problematic experiences with technology, negative feelings regarding a participant's couple relationship with their partner (studies B and D), or insufficient support for the upcoming labor and parenthood. In contrast, the use of the serious games may lead to positive effects on participants' feelings of being able to handle childbirth, parenthood, or the couple relationships with partners (studies A, B, and D). For example, expectant parents may perceive the interventions (*Childbirth Journey* and *Interplay*) as digital tools, and deem the information as trustworthy, because they are controlled and provided by healthcare professionals. Negative side effects, such as disappointment, and participant dropouts are to be examined, and we will use both qualitative and quantitative research to detect any possible deterioration, as well as in the subjective experiences of the participants. The prospective study shall follow the ethical regulations and guidelines outlined in Swedish law and the Code of Ethics of the Declaration of Helsinki (52). Personal data shall be processed in accordance with the EU General Data Protection Regulation (53) and only the research manager has access to the participant identities. The participation is voluntary and written informed consent shall be obtained from all participants. The participant identities will be handled with confidentiality and the data material will be stored in ways that only allow the researchers access. The participants will not be provided any reimbursement for participation in neither of the studies. This study has been approved by the Regional Ethical Review Board in Gothenburg, Sweden (Dnr: 2020-01689).

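### As described, Study D's log data cannot be linked to a participant's questionnaires, so the planned association between use of Interplay and the questionnaire scores cannot be computed from the logs

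*Protocol article*

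**What the plan says.** All places are in the protocol article.

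- **Objectives, aim 4 (Study D):** "Parents' user behavior over time and individual sessions in" Interplay, listed alongside relationship quality, social support and sense of coherence.
- **Interventions, Interplay:** Study D will explore user behaviour, "as well as associated factors between parents' user behavior and experiences from" Interplay and those same three constructs. This is where the association between use and scores is stated.
- **Data Collection, log data:** "For studies B–D, log data for process evaluation purposes during the intervention will be collected". On content: "Only pre-specified log data will be collected, and they will not contain any information that can be used to identify individual participants". The article adds that this rules out recording IP addresses. On analysis: "Participants' mobile application usage will only be studied and presented through aggregated metrics, such as average session duration".
- **Data Collection, questionnaires:** QDR36, SOC-13 and the social support scale are completed at baseline and 6 months later. Other questions for Study D are left open until Studies B and C have reported.
- **Statistical Analyses:** questionnaire answers go into SPSS for comparisons and associations, controlled for covariates such as gender, age and education. Log data are not mentioned.
- **Ethics and Dissemination:** "only the research manager has access to the participant identities".

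**The concern.** One section promises an analysis that another section's data rules do not allow. To relate use of Interplay to questionnaire scores, each parent needs a usage value held against that parent's own scores. The log paragraph excludes anything that identifies a participant, and it says that usage will be studied, not merely shown, in aggregate.

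If the app is built to that description, the log-based part of this Study D question is lost. It cannot be recovered later, because a log record without a code cannot be matched to a questionnaire once the data are in. An analysis plan written afterwards could not restore the link. The description is also a commitment about participants' data, so departing from it would need revised participant information and ethics approval.

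**Working it through.** No figure in the article has to be reproduced for this point, so the check sets the requirements of the analysis beside what the article provides.

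1. **What the association needs.** For participant *i*, a usage value *u_i* (for example mean session duration or number of sessions) and a score *y_i* (relationship quality, social support or sense of coherence). A correlation or regression uses the pairs (*u_i*, *y_i*). Adjustment for gender, age, education and the other covariates adds further participant-level columns, so the data must be one row per participant.

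2. **Where *y_i* and the covariates come from.** The two questionnaires, with up to 120 parents sought. Nothing stands in the way here.

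3. **Where *u_i* comes from.** The log data are the only stated source of usage in Study D. No self-reported usage item is named, although the questionnaire content is not yet final.

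4. **Can *u_i* be joined to *y_i*?** The logs hold nothing that identifies a participant, and no study code or matching step is described. As written there is no key on which to merge.

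5. **Does the meaning of aggregated rescue it?** There are two readings:
   - *Pooled over participants.* Usage is one number for the whole group. It does not vary between participants, so its correlation with any score is undefined.
   - *Averaged within each user.* Usage does vary between users, but step 4 still applies: the averages cannot be attached to questionnaire records without a code.

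   Both readings lead to the same result for log-measured use.

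6. **What remains computable.** Descriptive usage over time and per session, in aggregate; associations among the three scales; change in the scales from baseline to 6 months; and associations with any experience or use that the questionnaires themselves ask about.

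**The case against.** The best defence is that the article is a condensed account with loose wording. Its example, average session duration, can be computed per user. The non-identification sentence is explained in the article by the absence of IP addresses, and a random code arguably identifies nobody by itself. The two questionnaires must be matched per participant, so some coding scheme is already implied, and how the app log carries it could be left to a fuller document. The logs are collected for process evaluation and are never named as the exposure variable, and a self-reported usage item may still be added.

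Part of this stands. The authors may intend a coded log, and self-report is possible. But the text restricts how usage is studied as well as how it is presented, and that wording would have to change even if a code is intended. A code whose key leads to a participant's identity also sits badly with the non-identification sentence. This is a conflict between two stated commitments, not merely an omitted detail.

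A reader might infer more than the documents support:

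- *That Study D loses its stated power.* The Participants section does not say which variables the expected relationship of 0.4 concerns. Data Collection cites earlier associations of relationship quality with sense of coherence and with social support, so a correlation between scales is at least as natural a reading.
- *That this is Study D's main question.* Nothing in the article ranks it so, and aim 4 lists usage beside the scales without stating an association. Only the Interplay section does that.
- *That usage has no variance between participants.* This follows only if a single pooled value is kept.
- *That the interest in individual sessions contradicts aggregated metrics.* Session behaviour can be summarised in aggregate.
- *That a promised analysis of harm or dropout by amount of use is lost.* Ethics and Dissemination says that negative effects and dropouts will be examined, but promises no link to usage.

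**Conclusion.** The concern holds for log-measured use. As written, the association between use of Interplay and the three questionnaire constructs cannot be computed from the logs for any of the up to 120 parents, because there is no link to their questionnaire records and analysis of usage is limited to aggregates. The loss would be permanent once uncoded logs have been collected.

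The conclusion rests on two assumptions: that the log paragraph is followed literally, and that no linkage is laid down in a fuller document not shown here. If a coded log is already intended, the remedy is mainly to correct the text and the participant information.

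The effect is confined to this one association. Questionnaire-only analyses, any self-reported use added later, and aggregate descriptions of usage are unaffected. The sample-size statement is not shown to depend on it.

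**What to change.** Settle this before Study D starts, in one of two ways.

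**Keep the log-based association.** Amend the log-data paragraph of Data Collection so that each log record carries a random study code, with no name, IP address or device ID. The code links the record to the same participant's, and the same couple's, baseline and 6-month questionnaires. The research manager, who already has sole access to identities, holds the key. State that usage is analysed per participant and that aggregation applies to presentation only. Update the participant information and the ethics approval to match.

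**Keep the logs anonymous.** Leave the log paragraph as it is, restrict the association in the Interplay section to questionnaire-reported use, and add the necessary items to the questionnaires. This is the weaker option: self-report is unlikely to recover session-level behaviour.

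The first option costs a code field in the app log, revised protocol and consent wording, and an ethics amendment. Its small downside is that the logs become pseudonymised instead of anonymous data. The article already commits to processing personal data under the EU data protection regulation. Study D follows Studies B and C, so there is time to make the change.

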### Data Analysis

#### Qualitative Data Analyses

The qualitative data from interviews with parents and professionals will be transcribed verbatim and analyzed using phenomenography (42). When analyzing the interviews (A–C), phenomenographic analysis will be conducted to explore the participants' various ways of understanding their experiences from taking part of the interventions *(Childbirth Journey* and *Interplay)*. Within phenomenography, peoples' various ways of perceiving or understanding a phenomenon are explored, not the actual phenomenon itself, as in many other qualitative methods (42). For study A–C, data analysis will be carried out using the seven steps described by Sjöström and Dahlberg (42): familarisation, compilation, condensation, grouping, comparison, naming and contrastive comparison. Data will be scrutinized within the research team, which consists of researchers with complementary experiences from qualitative research on professional support and serious games, who will be able to judge the data interpretation. The results will be published in international scientific journals.

#### Statistical Analyses

Participant answers to the questionnaires will be transferred directly into the Statistical Package for the Social Sciences (SPSS), in which both descriptive and analytical analyses will be performed for comparisons and associations. Analyses will be controlled for such covariates as gender, age, education, marital status, length of parental couple relationship, and perceived economy. An alpha level of ≤ 0.05 will be accepted as significant. The prospective sample size is deemed to provide adequate statistical power for the analyses to be performed.

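### Study D's named covariates do not include the baseline score of the outcome, although it is collected, so self-selected use of Interplay could pass for an association with follow-up scores

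*Protocol article*

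**What the plan says.** The Statistical Analyses section of the protocol article is the only place that describes adjustment. It says that "both descriptive and analytical analyses will be performed for comparisons and associations", and then: "Analyses will be controlled for such covariates as gender, age, education, marital status, length of parental couple relationship, and perceived economy". It does not say whether the outcome is the six-month score, a change score or a repeated-measures response, and it names no model.

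On timing, the Data Collection section says that "participants will complete a web-based questionnaire at baseline (Q1) before receiving the intervention" and that "Another web-based questionnaire (Q2) will be sent to the participants 6 months after Q1". It adds that "some previously validated measures will be included in both Q1 and Q2", and names QDR36, SOC-13 and the multidimensional social support scale. Other questionnaire content is left open until Studies B and C are done.

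On the aim, the Objectives section (fourth aim) and the Interplay section set out to explore "associated factors between parents' user behavior and experiences from" the game on one side, and couple-relationship quality, social support and sense of coherence on the other. Every Study D participant receives Interplay, so there is no unexposed group.

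On usage data, the Data Collection section says of the app logs that "they will not contain any information that can be used to identify individual participants". It continues: "Participants' mobile application usage will only be studied and presented through aggregated metrics, such as average session duration".

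**The concern.** The six named covariates are socio-demographic or describe the background of the relationship. The pre-intervention value of the outcome is likely to be the strongest single predictor of its six-month value. It may also influence how much a couple plays a game about their relationship, because the amount of play is chosen and not allocated. If it is left out, two statements cannot be told apart: couples who were already doing well played more, and playing went with a better score later.

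The distinction matters for how the results are used. The Discussion says that findings from Studies A–D will shape further development of both games before a planned randomised trial. It also presents the study of user behaviour as a step towards showing that Interplay is beneficial. A selection pattern could be read as an early sign of benefit.

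**Working it through.** **Plan's own figures.** The plan gives no figure for baseline adjustment or its absence. Only the target of 120 parents (Participants section) is used here. The 0.4 relationship and minimum of 100 in that section do not enter.

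**Inputs.**
- n = 120, from the Participants section.
- a = correlation of use with the Q1 score. Not in the documents; assumed 0.2–0.4, with 0 as the reference case.
- b = correlation of the Q1 score with the Q2 score on the same scale. Not in the documents; assumed 0.5–0.7.
- No effect of use on Q2 once Q1 is given.

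**Step 1: spurious correlation when Q1 is omitted.** Under these assumptions corr(use, Q2) = a × b.
- Low: 0.2 × 0.5 = 0.10
- Middle: 0.3 × 0.6 = 0.18
- High: 0.4 × 0.7 = 0.28
- If a = 0, the product is 0 for any b.

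**Step 2: chance of declaring it significant.** By Fisher's z, two-sided 5%, the test statistic is centred on atanh(r) × √(n − 3), with √117 = 10.82.
- r = 0.10: 0.1003 × 10.82 = 1.09, rejection about 19%
- r = 0.18: 0.1820 × 10.82 = 1.97, rejection about 50%
- r = 0.28: 0.2877 × 10.82 = 3.11, rejection about 88%

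Allowing for six covariates (√111 in place of √117) gives about 19%, 48% and 86%.

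**Step 3: check by simulation.** 3,000 runs per case, n = 120, least squares with six covariates generated independently of the scores.

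| a | b | False rejection, Q1 omitted | False rejection, Q1 included |
|---|---|---|---|
| 0 | 0.6 | 4.7% | 4.6% |
| 0.2 | 0.6 | 24% | 5.6% |
| 0.3 | 0.6 | 48% | 5.5% |
| 0.3 | 0.7 | 61% | 5.0% |
| 0.4 | 0.7 | 87% | 5.2% |

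**Step 4: does an unadjusted change score avoid the problem?** With equal variances, corr(use, Q2 − Q1) = (ab − a)/√(2 − 2b). At a = 0.3, b = 0.6 this is (0.18 − 0.30)/√0.8 = −0.13, rejected about 30% of the time. The bias remains and its sign reverses. With the outcome form unstated, the direction of a reported association could depend on that choice.

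**Step 5: precision.** Adding Q1 cuts the residual variance, but use and Q1 are then collinear. The variance of the use coefficient without Q1, divided by that with Q1, is (1 − a²b²)(1 − a²)/(1 − b²).
- a = 0.2, b = 0.5: 0.99 × 0.96/0.75 = 1.27
- a = 0.2, b = 0.7: 0.9804 × 0.96/0.51 = 1.85
- a = 0.4, b = 0.5: 0.96 × 0.84/0.75 = 1.08
- a = 0.4, b = 0.7: 0.9216 × 0.84/0.51 = 1.52

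The gain is thus equivalent to about 1.1–1.85 times the sample.

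**The case against.** Several objections have weight.

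- **The list is open.** The covariates are introduced as examples, and a condensed article may leave the full set to an analysis plan that is not shown. A reader might infer that baseline adjustment has been rejected. The text does not support that. What stands is that the one statement on adjustment gives a list and does not name this variable.
- **No regression of Q2 on use is stated.** Table 1 calls Study D longitudinal with repeated questionnaires, and a within-person comparison would use Q1. This stands in part: the plan leaves the choice open, and step 4 shows that using Q1 only through a change score is no safeguard.
- **A false association is not certain.** A reader might infer that the plan would produce one. It could; it does so only if use is related to the baseline score, and the documents say nothing on that.
- **Exploration is the stated purpose, and effects are left to the later trial.** This is fair. That better-functioning couples play more would be a legitimate result, but it should be reported as such and not merged with the association at six months.
- **As written, logged use cannot be joined to a person's scores.** This stands. Neither the vulnerable analysis nor the adjusted one can be fitted with unlinked, aggregate logs. The concern applies if use is self-reported, which the open questionnaire content permits, or if linkage is added. It applies equally to reported experience of the game.

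**Conclusion.** The point holds as a gap in specification, not as an error already built into a stated model. The named covariates omit a baseline score that the study plans to collect and that bears directly on the usage–outcome aim. Under the assumed correlations the spurious association is 0.10–0.28, with about 19%–88% false rejection at n = 120; it vanishes if use and baseline score are unrelated.

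Three limits apply. The rates treat 120 parents as independent and all followed up, whereas the exclusion criteria require both partners of a couple to take part. They also assume that the listed covariates carry none of the baseline quality; if they carry some, part of the bias is already absorbed. And adjustment removes the bias fully only so far as the Q1 score measures baseline quality without error. None of these weakens the case for naming the covariate: in the simulated case where it was not needed, including it left the false rejection rate near 5%.

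**What to change.** In the Statistical Analyses section, state that each Q2 outcome is modelled with its own Q1 score as a covariate, in addition to those listed, whenever it is related to use or experience of Interplay. Report the association between the Q1 score and use separately, as a finding about who plays.

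In the Data Collection section, reconcile the non-identifying, aggregate-only log data with the usage–outcome aim in the Objectives and Interplay sections. Either add self-reported use to the questionnaire, or link logs to questionnaires under a pseudonymous code, with the data-protection wording changed to match. Failing both, drop the person-level association with use from the aims.

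The covariate costs one sentence and one degree of freedom, and no new outcome data, since the three scales are already planned at Q1. The usage data cost more: extra questionnaire items, or a linkage procedure and any approval it needs. Study D follows Studies B and C, and its questionnaire content was still open when the article was written.
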